### Specific challenges in Indonesia

Indonesia is among the top three highest TB-burden countries internationally [2]. The results of a national TB prevalence survey revealed that TB prevalence among Indonesian adults was almost double previous estimates (759 vs 391 per 100,000 population) [17]. A previous evaluation of the implementation of child contact management in Bandung, Java, reported wide implementation gaps in the cascade of care with only 8% (34/437) of child contacts presenting for screening within 3 months of adult index case diagnosis [18]. This low uptake is similar to findings from elsewhere when contact management is “passive” and facility-based [19–21]. Now, an ambitious international target has been set for ≥ 90% of young TB-exposed children to receive preventive treatment by 2035 [22]. In response to this call, the Indonesian National TB Program has embraced contact management and investigation as an important component of the Indonesian TB program [1, 8, 23].

### Implementation science approaches in TB research

Too often, deployment of a new policy relies on the distribution of a clinical practice guideline without provision of adequate staff training, with resulting inadequate uptake. A systematic method incorporating knowledge of the barriers which need to be addressed, the behaviors which need to be changed, and strategies likely to be effective is needed to improve intervention design [24]. Validated theoretical frameworks and implementation strategies can be used in projects designed to bridge the policy-practice gap in TB contact management [25].

There is a strong culture of “operational research” in TB, sometimes used interchangeably with the term “implementation research” [26], to improve program performance [27]. But surprisingly, there is limited reported use of theory-derived frameworks in TB research. The Behaviour Change Wheel [24] has been applied to TB contact investigation in Uganda and found to be an effective strategy for identifying barriers to and facilitators of this policy [13]. The theory of planned behavior and the PRECEED model (“Predisposing, Reinforcing and Enabling Constructs in Educational Diagnosis and Evaluation”) have been successfully applied to improve the quality of TB care, also in Uganda [28]. However, few other studies report the application of theoretical frameworks in TB operational research. A systematic review identified that theoretical frameworks to underpin behavior-change interventions have been underutilized in general in the past [29]. There are increasing calls to research frameworks in these contexts to ensure that interventions are comprehensive, well-structured, and replicable [30].

In our study to implement contact management in Mimika district, Eastern Indonesia, we use the Consolidated Framework for Implementation Research (CFIR) [31] to identify current reasons for the lack of policy implementation and the COM-B model (“Capability, Opportunity, and Motivation Behaviour system”) of the Behaviour Change Wheel [24] as a means of categorizing activities required for successful policy implementation. We use the RE-AIM model (Reach, Effectiveness, Adoption, Implementation, Maintenance) [32, 33] as the evaluation framework.

The overarching objective of this health system strengthening research is to reduce TB rates in an under-resourced, high-burden setting, especially among infants and young children, by effectively implementing TB contact management. To facilitate policy implementation, change is required across three levels of the healthcare system—policymakers, healthcare providers, and patients and their families. The aim of this methods paper is to describe the protocol for this study, including theoretical underpinnings and methodological approaches. We describe context-specific barriers to and facilitators of TB contact management at the study site using the CFIR and map these to the Behaviour Change Wheel.

## Methods

This is a mixed-methods, before-and-after intervention study, using interrupted time series (ITS) analysis. Activities fulfill the definition of a complex intervention (Table 1) [34]. A suite of interventions will be implemented in a staggered way over 24 months, independent of other changes in the TB program. The study is led by a collaborative investigator group in Indonesia and Australia and registered with the Australian New Zealand Clinical Trials Registry (trial ID: ACTRN12618001503213) [35]. At the field research site, two study nurses are employed as research assistants and data managers. They are supervised by a local medical doctor currently enrolled as a doctoral research scholar (TL) who lives on site as the main study implementer. The strength of relationships between the research team with stakeholders and healthcare providers contributes importantly to feasibility.

**Table 1 Tab1:** Alignment of study activities with Medical Research Council UK measures of intervention complexity

Characteristic of activities	Extent to which the study activities are complex
Number of interacting components within the experimental and control interventions	Activities include: **•** Education and training **•** Continuous quality improvement workshops **•** Provision of medication There is a retrospective control period and a prospective experimental period.
Number and difficulty of behaviors required by those delivering or receiving the intervention	Health care providers need to significantly change practice to start doing contact investigation, which was not previously undertaken: **•** Details of contacts need to be documented on a new TB form. **•** Contacts need to be seen by healthcare providers, assessed, investigated appropriately, commenced on medication as appropriate, and followed up for at least 6 months. **•** Patients need to adhere to medication and medical follow-up appointments.
Number of groups or organizational levels targeted by the intervention	Five healthcare facilities (phase 1 implementation) Seven healthcare facilities (phase 2 implementation) District TB Program District Health Authority
Number and variability of outcomes	There are six main outcomes: Primary: **•** Number of individuals completing isoniazid preventive therapy (IPT). Secondary (numbers and proportions of): **•** Index cases for whom contact investigation and management is undertaken **◦** All **◦** Smear-positive **◦** Smear-negative **•** Contacts reached for symptom screening **•** Contacts found to have active TB **•** Contacts eligible for IPT **•** Contacts commencing IPT.
Degree of flexibility or tailoring of the intervention permitted	A degree of tailoring is permitted since healthcare facilities differ (hospitals, primary care sites, rural, urban, etc.)

Factors listed in the left hand column are derived from Craig et al [34]

### Setting

Mimika district, population 201,677, spans from the coastal to highland areas in southern Papua Province, Indonesia [36]. Mimika is characterized by ethnic contrasts, challenges of multiple languages, geographical isolation of remote communities, poverty, and poor health outcomes [36, 37]. Proceeds from a large gold and copper mine fund some private clinics and hospitals. The estimated incidence of notified active TB cases in Mimika district in 2017 was 743/100,000, compared with the national incidence of 391/100,000 [17]. HIV-TB coinfections and late presentation with advanced disease are both common [38, 39]. The estimated proportion of TB cases that are multidrug resistant (MDR) has risen from 1.3% in a study of pulmonary TB patients with initial presentations in 2008–2010 [40] to 2.4% among new cases and 13% among retreatment cases in 2018 [2].

### Model for clinic participation in study implementation

The study will use a two-tiered approach for policy rollout, comprising initial clinics receiving intensive intervention and follow-up clinics receiving less intensive intervention (Fig. 1). The intention is to generate a “ripple effect” from the initial sites out to a wider catchment. Of 23 primary health centers (PHCs) and 5 hospitals in Mimika district, 10 PHCs and four hospitals are authorized to provide TB diagnosis and management, free of charge. Five sites were initially invited to participate based on their TB burden and location. We purposively selected a mix of urban and rural, private and public, and primary and tertiary sites and included those with largest caseloads. All agreed to participate. Characteristics and locations are shown in Table 2 and Fig. 2. The remaining seven PHCs providing TB care in Mimika will be invited to receive a less intensive follow-up intervention.

**Fig. 1 Fig1:**
[figure not shown]
Conceptual diagram of study implementation. Intensive intervention is delivered at the five initial sites by the research staff. Second-tier intervention is carried out at the seven follow-up sites by staff from the primary sites

**Table 2 Tab2:** Characteristics of study sites and 2017 TB case load at the five initial participating sites

	TB case burden (2017)	Governance	Location	Number of TB nurses	Number of doctors	Number of beds
Hospital 1	228	Private	Rural	3	2	144
Hospital 2	577	Public	Urban	3	2	159
Primary healthcare center 1	47	Public	Rural	3	1	0
Primary healthcare center 2	192	Public	Urban	5	2	20
Primary healthcare center 3	43	Public	Urban	4	1	2

**Fig. 2 Fig2:**
[figure not shown]
Map of Papua showing Mimika district in Papua province and participating study sites. Blue points are participating hospitals, red points are participating health centres, green points are second-phase participating health centers, and black points are non-participating centres

### Quantitative data collection and methodological approach

#### Data sources

Participating PHCs and hospitals maintain standard national data forms (Table 3), which will be used as the quantitative data for this study to complete the “cascade of care,” illustrating numbers of cases eligible for contact tracing, and losses occurring in each subsequent step. Sources and methods of data collection before and after interventions will be the same, except for additional use of new standard forms for child TB screening (TB15) and TB contact investigation (TB16) that were not available at the study sites before the intervention started. The research nurses will assist in the completion of the TB15 form initially, aiming for this task to be taken over routinely by healthcare providers as they become accustomed to it. Data of all TB cases from five initial participating centers will be collected every 2 weeks and checked for completeness. Cross-checking against original sources will be undertaken where data are incomplete, and TB staff will then be asked to complete missing data. Additional data validation will be undertaken from each participating site every 3 months to determine data reliability. Data from the seven other health facilities which receive less intensive intervention will be collected monthly.

**Table 3 Tab3:** Quantitative data collection: data sources and estimated sample size during the intervention phase

Sources of quantitative data	
Form type	Name of form
Individual TB treatment card detailing diagnosis date, adherence and number of contacts	TB01
Register of all TB patients at a health facility	TB03
Laboratory register for smear sputum TB examination	TB04
Register of all people suspected of having TB	TB05
Form for child TB screening	TB15
Register of TB contacts at a health facility	TB16
Sample size	
Step of management cascade	Estimated sample size at the 5 primary sites in 24 months
Estimated number of index cases	2000
Estimated number of contacts	10,000
Estimated number of contacts reached during the study: 40%	4000
**•** Estimated number of contacts found to have co-prevalent active TB: 5%	200
**•** Estimated number likely to require TB preventive therapy (15%)	600
**◦** Estimated number commencing on IPT (60%)	360
**◦** Estimated number completing IPT (60%)	216
Estimated number of TB cases prevented through IPT	6

Individual participant consent will not be sought for quantitative data, since this is routinely collected by health services. Research staff will enter these data into an electronic database. The cleaned primary data will be double entered into Stata version 13.0. The two datasets will then be compared, differences identified and corrections made.

#### Quantitative study design

The primary outcome measure is the number of individuals completing IPT abstracted from individual patient records. Secondary outcomes are the successive components of the cascade of care, namely numbers and proportions of index cases for whom contact investigation and management is undertaken (sub-grouped by smear-positive and smear-negative index cases), contacts reached for symptom screening, contacts evaluated for TB disease, contacts diagnosed with TB disease, contacts treated for TB disease, contacts eligible for IPT, contacts commencing IPT, and contacts completing IPT. During the available follow-up period, data will also be collected on the number, if any, of individuals commenced on IPT who develop TB disease (Fig. 3).

**Fig. 3 Fig3:**
[figure not shown]
Cascade of care showing estimated numbers of contacts at each step of the cascade associated with the expected 2000 TB index cases during 24 months. *PT* preventive therapy

Data on variables with the potential to affect outcomes will be collected and classified as study-related activities (categorized according to the COM-B model), external activities (e.g., introduction of a new recommendation by the provincial health authority), and environmental influences (e.g., holiday periods, major weather events, political unrest).

#### Study population

The study population for the quantitative data collection comprises TB index cases (people diagnosed with pulmonary TB) and their household contacts, using the WHO definition of a household contact [5, 41]. When the index case commences TB therapy, or later during treatment if the initial opportunity was missed, they will be asked to provide a list of household members and will receive an explanation that the public health team at the PHC will visit the household for contact investigation and management.

### Estimated sample sizes for contact investigation and preventive therapy

Numbers are provided in Table 3 showing the following minimum estimates: index case numbers per year, number likely to have contact investigation undertaken during the study period, number of contacts reached, number of contacts eligible for commencing and completing IPT, estimated number of cases of TB disease found during active case finding, and estimated number of TB cases averted. In Mimika, there are at least 1500 adult cases of TB notified annually, 1000 of whom are estimated to be managed at the five primary participating sites. We estimate up to five contacts per household, giving 10,000 individuals eligible for contact tracing over 2 years (Fig. 3).

We estimate that 40% of contacts (*n* = 4000) will be reached overall (aiming to progressively increase the two-year intervention from the baseline of zero contacts being reached); 5% of contacts reached will have co-prevalent active TB identified (*n* = 200); 15% of contacts reached will be eligible for TB preventive therapy (*n* = 600); 60% of those will commence on IPT (*n* = 360); 60% of those commencing IPT will successfully complete the 6-month regimen (*n* = 216) (Fig. 3). If the number needed to treat and to prevent a TB case is 35 [6], then for 216 people completing IPT, 6 TB cases will have been prevented.

These estimates are derived from previous studies of co-prevalent and incident tuberculosis and IPT [6, 11, 42, 43]. The proportion of child household contacts identified as having clinically or microbiologically diagnosed active TB during 12-month investigation periods was 7.8% in an Indonesian study [11] and 10% in an Ugandan study [42]. The proportion of all (adult and child) contacts with microbiologically confirmed TB in a household study in India was 6.9%, with about two thirds of these cases being co-prevalent—that is, picked up on initial household screening—and one third developing during the following 12 months (IPT was not given) [43]. This is why 5% has been estimated as the proportion of contacts who will be found to have co-prevalent active TB. The proportion eligible for IPT (no active TB and child aged < 5 or an immunosuppressed person of any age) is derived from the Indonesian study [11].

These numbers will provide good power to observe trends in clinic performance over time relating to child contacts being screened and treated appropriately and to undertake before-and-after calculations.

### Data analysis

Interrupted time series analysis will be used to analyze longitudinal time-dependent data. Study periods comprise a 26-month retrospective baseline period from 1 January 2015 to 31 March 2017, a 5-month prospective baseline period with active data cleaning and validation, a 24-month intervention period (including activities at initial and follow-up sites), and a 12-month sustainability period (Fig. 4). These periods were chosen pragmatically on the basis of available data and timing of study commencement. An annotated line graph, created with quarterly data points, will be produced to show the primary outcome (numbers of people completing IPT) over time, with the timing of key study activities, external activities, and environmental influences being indicated on the graph.

**Fig. 4 Fig4:**

Timeline

Segmented regression will be used to measure immediate changes in the rate of the outcome as well as changes in the trend. Calculation of rates will include 95% confidence intervals for the point estimates of rates in each time period. Crude rate will be calculated separately for intervention sites and non-intervention sites. It is assumed that populations of children in close contact with a TB patient in the intervention and non-intervention sites are comparable. The difference in rates will be calculated to estimate how the change in the intervention population differed from the change in the control population over the same time period.

AutoRegressive Integrated Moving Average (ARIMA) modeling will be used to test for any changes following the implementation of the program. Stationarity will be assessed and confirmed using the Augmented Dickey-Fuller (ADF) test on the log-transformed and re-plotted data. The data will be judged stationary with the *p* value of the ADF test < 5% level of significance. To choose the *p* and *q* parameters of the ARIMA, two diagnostic plots, i.e., autocorrelation function (ACF) and partial autocorrelation function (PACF), will be created as bar charts. The 95% confidence intervals will be shown as horizontal lines, and bars that cross these confidence intervals are therefore worth noting. The estimated value of *p* and *q* is the last lag with a large value if the autocorrelations (*q*) and partial autocorrelations (*q*) cut off after a few lags. A mixed model is suggested when neither the autocorrelations nor the partial autocorrelations cut off. Diagnostic checking of the model will be done once the model has been fitted.

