How will I and the intervention reach the targeted population? Reach is the absolute number or proportion of individuals who are willing to participate in a given initiative.	• Project staff will visit clinics directly and meet with relevant local stakeholders. We already have support and permission from relevant local authorities to undertake the study. • TB staff at the participating health facilities will be trained in workshops and informal on-the-job interactions to undertake the intervention, comprising identifying TB symptoms and asymptomatic TB contacts, referral, education of patients, prescribing, and monitoring. • Project staff will also have direct contact with selected, consenting TB patients and their contacts through referral by clinic staff, for interviews and provision of education.	• Proportion of health providers who participate in the intervention • Uptake of contact investigation among smear sputum positive TB individual • Uptake of preventive therapy among child contact of smear sputum positive TB cases
How do I know my intervention is effective? Effectiveness is the impact of an intervention on outcomes, including potential negative effects, quality of life, and economic outcomes.	• Relevant data will be collected regularly. The listed quantitative outcome measures will demonstrate whether interventions are working • Results of staff interviews will show whether staff have adequate knowledge of the process of contact management, and whether they are satisfied with the project.	• Significant change in the practice of contact investigation and preventive treatment identified using ARIMA model • Number of new TB cases (adult and children) identified from contact investigation • Number of children eligible for preventive therapy identified from contact investigation • Number of eligible children commence on preventive therapy • Adherence to preventive therapy among eligible contacts

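### The ARIMA test of change requires logs of a series that the plan puts at zero throughout baseline, so that step cannot be carried out as written

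*Protocol article*

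**What the plan says.** The primary outcome is a count: "The primary outcome measure is the number of individuals completing IPT abstracted from individual patient records" (Quantitative study design). The secondary outcomes are the other steps of the contact cascade.

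The Data analysis section plans two things for these series. One is segmented regression for changes in level and trend, with crude rates and 95% confidence intervals. The other is the test: "AutoRegressive Integrated Moving Average (ARIMA) modeling will be used to test for any changes following the implementation of the program". For that test it fixes the preparation, "Stationarity will be assessed and confirmed using the Augmented Dickey-Fuller (ADF) test on the log-transformed and re-plotted data", and the decision rule, "The data will be judged stationary with the *p* value of the ADF test < 5% level of significance". It states no offset and no other treatment of zeros.

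Table 6 lists five effectiveness indicators. The first is "Significant change in the practice of contact investigation and preventive treatment identified using ARIMA model".

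On the baseline, the section on estimated sample sizes describes an increase "from the baseline of zero contacts being reached". Table 1 says the same from the practice side: "Health care providers need to significantly change practice to start doing contact investigation, which was not previously undertaken".

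**The concern.** A contact who was never reached cannot be screened, found eligible, started on IPT or complete it. If no contacts were reached before the intervention, the primary outcome and all contact-level secondary outcomes are zero throughout the baseline, and the log of zero does not exist. The only method that the article names as a test of change therefore meets undefined values over nearly half of its series.

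This is not a detail left to a fuller plan. The article fixes the transformation, the stationarity test and its 5% rule, and it also states the baseline that makes them unworkable. The practical risk is that someone adds a constant, or drops the log, once the data are in view. The effect size then depends on a choice that nobody recorded in advance.

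**Working it through.** **1. The plan's own expected figure.** From Table 3 and the sample-size section: 2000 index cases × 5 contacts = 10,000; × 0.40 reached = 4000; × 0.15 eligible = 600; × 0.60 starting = 360; × 0.60 completing = 216. This reproduces the stated 216. The same product with none reached gives 0 at every later step, which is the baseline.

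**2. Length of the series.** The article gives a "26-month retrospective baseline period from 1 January 2015 to 31 March 2017". Those dates span 27 months. With the 5-month prospective baseline, the baseline is 26 + 5 = 31 or 27 + 5 = 32 months. Adding 24 intervention and 12 sustainability months gives 67 or 68 months, about 22 quarters. Quarterly spacing is stated only for the graph.

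**3. Share of the series that cannot be logged.**
- Monthly: 31/67 = 46%, or 32/68 = 47%.
- Quarterly: about 10/22 = 45%.
- If completions are dated at the end of the 6-month regimen (an assumption), the first 6 intervention months are also zero: 37/67 = 55%, or 38/68 = 56%.

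**4. The step as written.** I took a quarterly series of 10 zeros, then 216 completions rising linearly over 8 quarters (6, 12, …, 48), then 4 quarters at 48. The linear rise and the plateau are assumptions. The log gives minus infinity at 10 of 22 points, and the ADF routine stops with an error. The monthly version also fails.

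**5. An exactly zero baseline is not needed.** One zero is enough. If baseline completions were Poisson with mean m per quarter (assumed values), the chance of at least one zero in 10 quarters is 1 − (1 − e^−m)^10:

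| m | chance |
|---|---|
| 0.5 | >99.9% |
| 1 | 99% |
| 2 | 77% |
| 3 | 40% |

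**6. What an offset k does.** The post-baseline mean in step 4 is (216 + 4 × 48)/12 = 34 per quarter. The average log step is log(34 + k) − log(k):

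| k | step |
|---|---|
| 0.01 | 8.13 |
| 0.1 | 5.83 |
| 0.5 | 4.23 |
| 1 | 3.56 |

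The data are the same in every row; only the constant differs. Fitted models show the same dependence. In one simulation with a gradual rise, the estimated step ran from 0.73 (k = 1) to 2.27 (k = 0.01). The exact values depend on the assumed shape.

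**The case against.** **The rest of the evaluation survives.** This stands. The segmented regression and crude rates are not stated to use a log. ARIMA is one of five effectiveness indicators, and the other four are counts and adherence. A reader might infer that the whole assessment of effectiveness collapses; the article does not support that.

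**The ADF rule would block ARIMA even with an offset.** A reader might infer this too, because with an offset the undifferenced simulated series often fail the rule. In one set of runs none passed; across other quarterly settings 0 to 61% passed, depending on the shape of the rise and the completion lag. But failing the ADF test ordinarily leads to differencing, which is what the integrated part of ARIMA means. After one difference, 66 to 100% passed across the settings tried. So the rule is not an absolute barrier.

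**Differencing would reduce the effect to a single pulse.** This does not hold. The step regressor is differenced along with the outcome, so its coefficient still estimates the level change.

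**A fuller plan may add an offset, or the retrospective records may hold a few completions.** The first is possible, but the published step still conflicts with the published baseline. The second does not rescue the log unless completions were frequent enough to leave no empty period (step 5 of the working).

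**The article does not name the series to be logged.** True. The count of index cases is not zero at baseline, but it is not an outcome of the intervention. Every contact-level outcome is zero under the stated baseline.

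**Conclusion.** The concern holds for the ARIMA step. On the plan's own baseline, 31 to 32 of 67 to 68 months, or about 10 of 22 quarters, have no logarithm, and the article gives no rule for them. The named test of change cannot be run as written on the primary outcome or on any contact-level outcome. Any offset added later moves the estimate materially, by a factor of more than two on the log scale in the illustration (8.13/3.56 = 2.3).

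Two assumptions carry this. Zero completions follow from zero contacts reached through the cascade; the article does not state them as a separate figure. The sizes in step 6 rest on an assumed linear rise to the planned total. The higher share of 55 to 56% applies only if completions are dated at the end of the regimen.

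**What to change.** - **Test of change.** Drop the log, ADF and ARIMA sequence in that role. Use the segmented regression already planned, on untransformed counts or rates per index case registered in TB03, with a count model and autocorrelation-robust errors.
- **All-zero baseline.** Estimate neither a baseline slope nor a ratio to baseline. A log-link count model has no finite step against zeros, so it should describe the intervention and sustainability periods only. Report the baseline as 0 with an exact upper confidence limit. Report the rate, the trend and the absolute rate difference from baseline for the intervention and sustainability periods, with confidence intervals.
- **ARIMA, if kept.** Run it on the unlogged series as a sensitivity analysis, with the differencing rule fixed in advance.
- **Table 6.** Reword the first effectiveness indicator to match.

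The absolute scale loses little here. Suppose the planning figure of 1000 index cases a year at the five sites also held at baseline (an assumption). Over 31 months that is 1000 × 31/12 = 2583 index cases. With no completions, the exact Poisson upper limit (two-sided 95%) is −ln(0.025) = 3.69 completions, or 3.69/2583 = 1.4 per 1000. The planned intervention rate is 216/2000 = 108 per 1000.

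The cost is some rewording of the analysis section and one table entry, and the loss of a ratio-type effect against baseline. No new data are needed, since TB03 is already a listed source. The change should be dated and made before the outcome series is analysed.

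### The stationarity test for the ARIMA analysis is specified on log-transformed data, but the plan's own baseline is zero, so most or all baseline values have no logarithm and the step cannot be run as written

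*Protocol article*

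**What the plan says.** The outcome is a count: "The primary outcome measure is the number of individuals completing IPT abstracted from individual patient records" (Quantitative study design). The Data analysis section plans segmented regression of rates and a difference in rates between intervention and non-intervention sites. Separately, it says that ARIMA "modeling will be used to test for any changes following the implementation of the program". In that ARIMA paragraph the order is a stationarity check, then the choice of p and q, then fitting and diagnostics. The stationarity check reads "Stationarity will be assessed and confirmed using the Augmented Dickey-Fuller (ADF) test on the log-transformed and re-plotted data". No rule for zeros, added constant or other scale is given.

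Two other places describe the baseline. The sample-size section speaks of progressive increase "from the baseline of zero contacts being reached". Table 1 says providers must "start doing contact investigation, which was not previously undertaken".

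Table 6 lists, among its effectiveness indicators, "Significant change in the practice of contact investigation and preventive treatment identified using ARIMA model".

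**The concern.** The logarithm of zero does not exist. If the baseline series consists of zeros, the logged series has no usable pre-intervention segment, and the test that opens the ARIMA procedure cannot be computed. An analyst then has two ways out. One is to let the software treat the undefined values as missing, which leaves nothing before the intervention to compare with. The other is to add a constant before taking logs, in which case the size of the reported change depends on a number that the article does not fix. At stake are the interpretability of a named effectiveness indicator and the differencing decision on which the ARIMA model is built.

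**Working it through.** **1. The plan's own figure.** From Table 3 and the sample-size section: 2,000 index cases × 5 contacts × 0.40 reached × 0.15 eligible × 0.60 starting × 0.60 completing = 216 completions in 24 months. This reproduces the stated 216. Spread evenly over 8 intervention quarters, it is 216 / 8 = 27 per quarter.

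**2. Number of points.** The baseline is described as "a 26-month retrospective baseline period from 1 January 2015 to 31 March 2017, a 5-month prospective baseline period". That is 26 + 5 = 31 months, or 10 full quarters (the stated dates span 27 months, which does not change the count). The intervention gives 8 quarters and the sustainability period 4, so 22 in all. Quarterly spacing is stated only for the graph ("An annotated line graph, created with quarterly data points") and is assumed here for the analysis. With monthly points the baseline would still be zero.

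**3. How many points have no logarithm.** With no contacts reached there are no contact completions, so 10 of 10 baseline quarters are undefined. The regimen lasts 6 months, so about 2 early intervention quarters are probably zero as well: 12 of 22, or 55%. If two isolated baseline completions occurred in different quarters (an assumption), 8 of 10 baseline quarters would still be undefined. Run on the raw logged series, the ADF test stops with an error because of the infinite values.

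**4. Effect of an added constant on the size of the change.** From a baseline of 0 to 27 per quarter, the log-scale contrast is ln((27 + c)/c).

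| c | (27 + c)/c | log contrast |
|---|---|---|
| 1 | 28 | 3.33 |
| 0.5 | 55 | 4.01 |
| 0.1 | 271 | 5.60 |
| 0.01 | 2,701 | 7.90 |

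**5. Effect on the tests.** The article gives no quarterly pattern, so two assumed patterns were tried, each with a zero baseline and 216 completions in the intervention period.

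- Prompt uptake: 6, 12, …, 48, then 48 in each sustainability quarter.
- Delayed uptake: 0, 0, 12, 24, 36, 42, 48, 54, then 54 in each sustainability quarter.

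The ADF test used one lag. Level and slope changes come from ordinary least squares on ln(count + c), with the slope change counted from zero at the first intervention quarter.

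| Pattern | Quantity | c = 1 | c = 0.001 |
|---|---|---|---|
| Prompt | level-change ratio | 12.8 | about 11,700 |
| Prompt | ADF p, first difference | 0.14 | 0.044 |
| Delayed | level-change p | 0.057 | 0.043 |
| Delayed | slope-change p | 0.003 | 0.018 |
| Delayed | ADF p, first difference | 0.11 | 0.046 |

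At the plan's 5% criterion, the constant alone moves the differenced series from non-stationary to stationary in both patterns. With delayed uptake it also moves the level-change p-value across 5%, by a narrow margin that depends on how the slope term is coded. The slope change is significant throughout. With prompt uptake the level change is also far below 5% at every constant.

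**6. Exact limit for a zero baseline.** With 0 events, the two-sided 95% Poisson upper limit is −ln(0.025) = 3.69 events for the whole baseline.

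**The case against.** Much of the case on the other side stands.

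- **The log is tied in words only to the ADF step.** Fitting ARIMA on the same scale is the natural reading, because the ADF result feeds the model choice, but it is not stated. Even on the narrow reading the ADF step fails.
- **Zero completions is inferred.** The article states zero for contacts reached. A few people may have completed IPT by another route, so zero or nearly zero is the defensible wording.
- **Other analyses survive.** Segmented regression of rates, rates with confidence intervals, the difference in rates and the line graph involve no stated log. ARIMA is one of five effectiveness indicators in Table 6. The others (new TB cases found, eligible children, children starting therapy, adherence) need no logarithm.
- **A separate analysis plan may set a rule for zeros.** It is not shown. This answers any suggestion that a constant would be picked with the results in view. It does not answer the conflict in the article, which fixes the log and states the zero baseline.

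A reader might go further and infer that the whole before-and-after comparison is void, or that the verdict of change or no change rests on the constant. The documents do not support either. In simulated Poisson series with gradual uptake, analysed by segmented regression on ln(count + c), the slope change was significant in over 99% of runs at every constant tried. That log-scale regression is itself not in the plan, so its rejection rates for the level change should not be read as properties of the planned analysis.

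**Conclusion.** The concern holds for the ADF and ARIMA branch. It is a stated rule that fails on the plan's own inputs, not a detail left for later. As written, 10 of 10 baseline quarters have no logarithm if baseline completions are zero, and most have none if they are nearly zero. A workaround constant sets the reported effect size anywhere from 28-fold (c = 1) to 2,701-fold (c = 0.01). It can also change the stationarity decision and, when uptake is slow, the level-change p-value. Detection of a change in trend is usually not at risk.

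This rests on three assumptions: baseline IPT completions follow the stated zero for contacts reached, points are quarterly, and the model is fitted on the scale used for the ADF test. The fold-changes also take an even 27 per quarter. The p-values in the working belong to assumed uptake patterns and illustrate the dependence rather than predict it.

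**What to change.** Remove the log transformation for the primary outcome and for any other cascade count that is zero at baseline. Run the ADF and ARIMA steps on untransformed counts or rates, or on the residuals of the segmented model. Report level and slope changes as absolute counts per period, and report the baseline count with its exact Poisson limit (3.7 events for the whole baseline if none are seen).

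A count model is an acceptable alternative. In that case, prespecify an exact or penalised method for an all-zero baseline, because an ordinary rate ratio against zero is not finite.

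The cost is a sentence or two of analysis wording, with no change to data collection or design.
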